## Analysis Sets

Of all research subjects enrolled in this study, the population will include the study subjects, excluding significant deviations from the following study protocol:

- Incompatibility of inclusion criteria
- To meet the exclusion criterion

## Analysis of Baseline Survey Items

Frequency tables will be generated for categorical variables and summary statistics (number of subjects, mean, standard deviation, minimum, median, and maximum) will be obtained for continuous variables.

1. Distribution of background factors
2. Type, administration, and number of daily doses of anticoagulation used at enrollment
3. Type of antiplatelet drug used at the time of enrollment
4. Types of other concomitant medications used at the time of enrollment
5. CHADS scores (Appendix 1) or the CHA _2_ DS _2_-VASc scores (Appendix 2) calculated from patient data at enrollmentAppendix 11Appendix 22

## Analysis of follow-up data

Frequencies and event rates and their 95% confidence intervals will be calculated for the following items:Cox proportional hazards models and logistic regression analysis are used to search for risk factors.

1. Type, dose, number of daily doses, and frequency of changes of anticoagulants and antiplatelet agents [at 12 and 24 months of follow-up]
2. Incidence of stroke/systemic embolism at 24-month follow-up

- Stroke (atherosclerotic, cardiogenic, lacunar, haemorrhagic, unclassifiable, other stroke, TIA)
- Systemic embolism

1. Incidence rate of bleeding adverse events [at 24-month investigation] (see Table 4 for classification of bleeding and definitions)Table 44

- Major bleeding
- Clinically relevant bleeding
- Minor bleeding
- Intracranial hemorrhage
- Gastrointestinal bleeding (upper and lower)

1. Number of falls
2. Incidence of bone fractures
3. Mortality (all deaths, cardiovascular deaths, non-cardiovascular deaths)
4. Incidence of myocardial infarction, cardiac intervention, and heart failure requiring hospitalization

(1) For ~(7), the CHADS score, the CHA _2_ DS_2_-VASc score, the HAS-BLED score and its constituent factors, the factors identified as risk factors in the guideline, the factors identified as risk factors in the present study, the presence or absence of anticoagulant therapy and type (DOAC, warfarin), dosage, PT-INR, etc. will be examined by subgroup.

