# Number of target registrations of study subjects

30,000 patients (consecutive enrollment) in the study as a whole

Rationale for target enrollment

The incidence of stroke/systemic embolism in Fushimi AF Registry's ^5^ has been reported to be 5.1/100 patients aged 85 years or older, 2.0/100 patients aged 84 years or younger, and a hazard ratio of 1.77 for patients aged 85 years or older to patients aged 75 years or older and 84 years or younger.

Based on this assumption, the incidence rates in patients aged 75 to 84 years and those aged 85 years and older are 2.9 per 100 person-years and 5.1 per 100 person-years, respectively, and the overall incidence rate is estimated to be about 3.5 per 100 person-years, assuming a patient composition ratio of 3:1 in this study.

We estimate the incidence of stroke/systemic embolism in patients without risk factors for this study to be 3.4/100 person-years. Assuming an exponential distribution (constant hazard) in time to onset, if the proportion of patients with risk factors is 5%, enrolling 30,000 patients will detect a hazard ratio of 1.3 for the development of stroke/systemic embolism with risk factors to no risk factors over a 2-year follow-up period of at least 5% with a two-sided significance level of at least 80% power.

For 30,000 patients, the power of 80% is to detect risk factors with a hazard ratio of about 1.5, even for intracranial hemorrhage, which is a low incidence but of particular concern, among the events planned to be studied. An estimated incidence of 1.2% per year of intracranial bleeding and a risk factor of 5% were assumed [e.g., a potential intracranial bleeding risk of 1.5 times greater than that of patients without SRI in patients with severe renal dysfunction (SRI)] would detect a statistically significant risk increase of 80% even with an SRI of about 5% of patients overall.

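### Protocol section 17.3 shows study-identified risk factors as subgroups on the events that selected them, so on that endpoint the ordinary 95% intervals lose coverage and the effects are inflated

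*Protocol*

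**What the plan says.** Section 17.3 (Analysis of follow-up data) fixes the output: "Frequencies and event rates and their 95% confidence intervals will be calculated for the following items". It names Cox and logistic regression as the tools for finding risk factors. Items (1) to (7) include stroke/systemic embolism, bleeding (with intracranial hemorrhage), falls, fractures, mortality and cardiac events. All of them are to be examined by subgroup, and one of the subgroup variables is "the factors identified as risk factors in the present study". The CHADS2, CHA2DS2-VASc and HAS-BLED scores and guideline risk factors stand in the same list, with no distinction between the two kinds.

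Section 13 (Number of target registrations of study subjects) sizes the study on detecting one factor at a time: "enrolling 30,000 patients will detect a hazard ratio of 1.3 for the development of stroke/systemic embolism with risk factors to no risk factors". For intracranial hemorrhage, "the power of 80% is to detect risk factors with a hazard ratio of about 1.5". The section on the purpose of the study makes identifying risk factors for these two endpoints an aim.

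**The concern.** A score or guideline factor is chosen without looking at this study's events, so its subgroup rates and intervals mean what they usually mean. A study-identified factor is chosen because its contrast in these same events was large. Showing that contrast again in the same patients adds no evidence, and an interval computed as if the factor had been fixed in advance ignores the selection.

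Identifying risk factors is a stated aim, so these are the factors that readers will look at most closely. In the table planned in section 17.3 they stand next to established factors in the same format. A reader could not tell which rows carry ordinary intervals and which carry selected ones. A chance finding at low prevalence could also look much like a true factor of the size the study was designed to detect.

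**Working it through.** **Inputs from section 13.** 30,000 patients; 5% with the factor; 2 years; constant hazard; 3.4 per 100 person-years for stroke/systemic embolism without the factor; 1.2% per year for intracranial hemorrhage. The wording on level and power is garbled ("over a 2-year follow-up period of at least 5% with a two-sided significance level of at least 80% power"); I read it as two-sided 5% and at least 80% power. No dropout or competing death is stated, so both are taken as zero.

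**The plan's own figure.** At a hazard ratio (HR) of 1.3:
- Exposed events: 1,500 × (1 − exp(−0.034 × 1.3 × 2)) = 127.
- Unexposed events: 28,500 × (1 − exp(−0.034 × 2)) = 1,874.
- SE(log HR) = √(1/127 + 1/1,874) = 0.092.
- Power = Φ(ln 1.3 / 0.092 − 1.96) = 81.6%.

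The same method gives 81.2% for intracranial hemorrhage at HR 1.5. Other formulas give 72.5% to 82.2% for the first figure and 66.5% to 81.9% for the second. The stated power is reproducible and is not disputed.

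**A factor with no effect, selected at p<0.05 in the harmful direction.** The threshold is my assumption. With E events and prevalence p, SE = 1/√(E·p·(1−p)). The mean log HR given selection is SE × φ(1.96)/0.025 = SE × 2.34.
- Stroke/systemic embolism: E = 30,000 × (1 − exp(−0.068)) = 1,972; SE = 0.1033 at 5%; mean HR = exp(0.1033 × 2.34) = 1.27.
- Intracranial hemorrhage: E = 30,000 × (1 − exp(−0.024)) = 711; SE = 0.172; mean HR = exp(0.172 × 2.34) = 1.50.

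Simulation of 200,000 studies per prevalence gave 1.25 for stroke/systemic embolism at 5%, slightly below the normal approximation. By prevalence:

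| Prevalence | Mean selected HR, stroke/SE (formula) | Mean selected HR, ICH (formula) | Exposed-group rate CI misses true rate, stroke/SE (simulation) | The two subgroup rate CIs do not overlap, stroke/SE (simulation) |
|---|---|---|---|---|
| 5% | 1.27 | 1.50 | 77% | 37% |
| 25% | 1.13 | 1.22 | 52% | 15% |
| 50% | 1.11 | 1.19 | 34% | 11% |

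The fourth column should read 5% if the intervals kept their nominal coverage.

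**Comparison with fresh events.** When the selected 5%-prevalence factor is assessed on independent events, its mean HR is about 1.00. It is significant again in the same direction in about 2.6% of cases.

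**True factors.** A real factor with HR 1.3 and 5% prevalence, once selected, shows a mean HR of about 1.36.

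**What a correction achieves.** For the chance stroke/systemic embolism factor at 5% prevalence, the uncorrected 1.27 falls to about 1.20 with a bootstrap optimism correction and to about 1.08 with 10-fold cross-fitting. Both help, and neither removes all the bias.

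**The case against.** The strongest reply is that section 17 defers detail to a separate statistical analysis plan, which is not at hand, and that thresholds, validation and labelling belong there. That is right for the selection threshold, and its absence is not criticised here. It does not cover the re-use itself, which section 17.3 states.

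A reader might infer that a chance factor will always look confirmed. The documents do not support that. It is exact only if the same unadjusted contrast is recomputed on the same endpoint. Section 17.3 reports rates with intervals, and for selected null factors the two subgroup intervals separate in only 11% to 37% of cases. A factor chosen in an adjusted model, or on one endpoint and tabulated on another of items (1) to (7), need not show the effect again.

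A reader might also infer that chance findings generally reproduce the design hazard ratio. That holds near 5% prevalence only. Close to half of chance selections also look protective. The likeness is partly generic: a null result selected at 5% averages about 2.34 standard errors, and an 80%-power target lies at about 2.8.

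The protocol does not present these subgroups as confirmation; it describes a search. It does not label them descriptive either. Lastly, how many false factors the search yields is a separate question. The number of candidates is not given, and the change proposed here would not alter it.

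**Conclusion.** The point holds in a limited form. Section 17.3 treats study-identified factors like factors fixed in advance. On the endpoint that selected them, the ordinary 95% intervals do not have nominal coverage and the displayed effects are too large. For a harmful-looking null factor at the design's 5% prevalence, the apparent HR is about 1.25 to 1.27 for stroke/systemic embolism and about 1.5 for intracranial hemorrhage; for stroke/systemic embolism at 25% to 50% prevalence it is 1.11 to 1.13.

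These sizes assume selection at two-sided p<0.05 on an unadjusted contrast, the section 13 event rates and complete follow-up. A different threshold or an adjusted search would change the numbers. The direction of the problem would remain as long as selection depends on the observed effect. The other factors in the list, and endpoints not used for selection, are outside this point. It should be corrected, but it does not undermine the search or the sample size.

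**What to change.** In section 17.3:
1. List study-identified factors separately from the scores and guideline factors.
2. For study-identified factors on their selecting endpoint, keep the crude subgroup rates and intervals, and label them as descriptive and not independent confirmation.
3. Beside them, report a selection-corrected HR with its interval and the selection frequency. Obtain these by cross-fitting (select in all folds but one, estimate in the one left out) or by repeating the whole search in each bootstrap sample. State that the correction is partial.
4. Leave the search itself unchanged.

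The cost is wording and some computing time. Effects for newly found factors will be smaller and their intervals wider. A half-and-half split of the cohort is not advised: about 1,000 events would remain for assessment, and power for HR 1.3 would fall to about 53% by the same Wald calculation.

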## Subgroup analysis (Sub-study 2)

Items to be examined by subgroup analysis are shown below.

1. By renal function (Ccr value)
2. By HbA1c
3. By the maximum number of drugs administered
4. Cases of ischemic heart disease
5. Cases of gastrointestinal bleeding
6. Cases of stroke

## Analysis of a subcohort study

Depending on the tabulated items, analyses will be conducted in accordance with Sections 17.2 and 17.3. A separate Statistical Analysis Plan should be followed for further analyses and for analyses not described below.17.217.3

### Sub-cohort study A: assessment markers

1. Distributions of PT; PT-INR; APTT; TTR; D-dimer; SFMC; F1+2; TAT; High-sensitivity troponin I; NT-pro BNP at baseline
2. Incidence of major bleeding, clinically important bleeding, and stroke/systemic embolism by TTR (warfarin administration patients) (at 24-month follow-up)
3. Incidence of major haemorrhage, clinically significant bleeding, and stroke/systemic embolism summarized by PT and APTT (at 24-month follow-up)
4. Incidence of major haemorrhage, clinically significant bleeding, and stroke/systemic embolism summarized by D-dimer, SFMC, F1+2, TAT, high-sensitivity troponin I, and NT-pro BNP levels at 24-month follow-up.

### Subcohort study B: Echocardiogram

1. Breakdown of underlying heart disease
2. Echocardiographic parameter values (at baseline) by type of NVAF (paroxysmal, persistent, permanent)
3. Echocardiographic parameter values (at baseline) by CHADS score and _2_ score.
4. Changes in Echocardiographic Parameters Over Time (Baseline, 12-Month, and 24-Month Surveys)
5. Echocardiogram defined factors (at baseline) in high _2_ scores of CHADS
6. Echocardiographic predictors of events, including stroke (at 24-month follow-up)

### Sub-Cohort Study C: Heart Rate

1. Distribution of heart rate (at baseline) during AF expression recorded on a 12-induced resting ELECTROCARDIOGRAM.
2. Changes in the frequency of AF recorded on 12-induced resting ELECTROCARDIOGRAM at baseline, 12-month follow-up, and 24-month follow-up
3. Changes in Heart Rate During AF Recorded on 12-Induced Resting ELECTROCARDIOGRAM (Baseline, 12-Month, and 24-Month Investigations)
4. Occurrence of Stroke and Systemic Embolism during AF Recorded by 12-Lead Electrocardiogram at Rest by Heart Rate (at 24-Month Investigation)

### Sub-cohort study D: Hypertension

1. Distribution of office blood pressure and home blood pressure values at enrollment (at baseline)
2. Incidence of stroke and systemic embolism based on distribution of office blood pressure and home blood pressure at enrollment (at 24-month survey)
3. Incidence of bleeding adverse events based on distribution of office blood pressure and home blood pressure at enrollment (at 24-month survey)

### Sub-cohort study E: cognitive function

1. Distributions of MMSE scores at different time points (baseline, 24-month survey)
2. Distribution of Social Activity at Enrollment (Baseline)
3. Change from Baseline in MMSE Score (Month 24)

### Sub-cohort study F: Frail

1. Percentage of frail and non-frail patients at enrollment (at baseline)
2. Patient Characteristics of Filled and Nonfrailed Patients at Enrollment (Baseline)
3. Frail and non-frail patients at enrollment, type of anticoagulant, dosage (DOAC only), and duration of treatment (at baseline)
4. Distribution of basic checklist evaluation values for the elderly (at baseline)
5. Distribution of questionnaires on living conditions (at baseline)
6. Incidence of stroke/systemic embolism by frail and non-frail patients at enrollment (at 24-month survey)
7. Incidence rate of bleeding adverse events by frail and non-frail patients at enrollment (at 24-month investigation)

### Sub-cohort study G: adherence

(1) Distributions of MMAS-8 scores at different time points (baseline, 24-month survey)

(2) Distribution of PDC (at baseline)

(3) Background Factors of Study Subjects with Improved MMAS-8 Scores (at Baseline and Month 24 Survey)

(4) MMAS-8 scores, comprehensibility of PDCs and NVAF, and their association (at baseline, at 24-month survey)

(5) Association of MMAS-8 scores with stroke/systemic embolism and hemorrhagic adverse events at 24-month follow-up

(6) Association between NVAF comprehensibility and stroke/systemic embolism and hemorrhagic adverse events at 24-month follow-up

(7) Association of PDC with stroke/systemic embolism and bleeding adverse events at 24-month follow-up

# Preparation and Submission of Case Report Form

## Format and Submission of Case Report Form

Investigations specified in this study protocol will be recorded on the Study Specific Case Report Form (eCRF). The format of the eCRF is as follows. The form will be entered at baseline, 12-month, and 24-month surveys and submitted (transmitted) promptly.

- Registration information for the study population
- Time of the baseline survey
- Months 12 and 24
- At withdrawal of consent and at the time of onset of adverse events, unless an emergent serious adverse event occurs.

## Method of creating the Case Report Form

Investigators and research collaborators shall access the EDC system dedicated to this study using the issued ID and password and enter the search information (the entry procedure for EDC shall follow the EDC entry manual, which is created separately).

# Monitoring and Auditing

## Monitoring and Auditing

The sponsor consults with the principal investigator to ensure the conduct of the study and the reliability of the records, and to ensure that the monitoring and audits are outsourced to the contract research organization, etc. Investigators and research institutions cooperate in monitoring and auditing. The principal investigator or others shall explain to the study subject that the source documents will be accessed by the monitors and the auditors and obtain consent from the subject in the Informed Consent Form.

## Monitoring

The monitors shall confirm that the study is conducted in compliance with the Ethical Guidelines for Medical Research Involving Human Subjects and the study protocol in accordance with the Monitoring Procedures developed separately. For direct access, the procedures specified in this study will be checked to check the source documents against those entered in the EDC to verify the integrity, accuracy and consistency of the collected data. After completion of the monitoring activities, a monitoring report will be prepared and reported to the principal investigator. In addition, the monitors shall divulge information obtained in the course of their duties without any justifiable reason, even after they have ceased to be engaged in the duties.

The research sponsor (Daiichi Sankyo Company, Limited) shall not be directly involved in the monitoring work in order to maintain the neutrality to this study.

## Auditing

The auditor maintains a standpoint independent of the monitoring duties and conducts written and on-site inspections in accordance with the Audit Operating Procedures prepared separately. The monitoring report shall be verified to ensure the conduct of the study and the reliability of the records thereof, and to guarantee this. Each investigator or sub-investigator shall, upon request of an auditor, provide all study-related records of the study subject for direct access. The auditor shall submit an audit report and an audit certificate to the principal investigator and the head of the study site. In addition, the auditor shall divulge information obtained in the course of his/her duties without justifiable reason, even after he/she has stopped engaging in the duties.

## Direct access to source documents

The director of a medical institution and the principal investigator provide direct access to the records related to clinical research, such as source documents, during monitoring, audits, and investigations by regulatory authorities and ethics review committees. The study sponsor (Daiichi Sankyo Company, Limited) does not conduct direct access.

# Ethic

This study will be conducted in accordance with the spirit of the latest Declaration on Helsinki by the World Medical Association, while protecting the human rights and welfare of the trainees, and in compliance with the Ethical Guidelines for Medical Research for Humans (MEXT, MHLW Notification No. 415 of 2014) ^24^ and related notices.^24^

## Ethical Review Board

After consultation with the principal investigator and the Study Central Committee, the sponsor will prepare a research protocol and informed consent form (sample) and obtain approval from an external ethics review committee designated by the research sponsor and from the Ethics Review Committee of the Cardiovascular Research Institute, which has jurisdiction over the Research Representative Facility. When the research protocol is revised, the research sponsor and the principal investigator shall prepare an revised version of the research protocol, etc. (informed consent form, if necessary) after requesting opinions from the Research Central Committee if necessary. After requesting and obtaining approval from the respective ethics review committees for reexamination, the revised version shall be implemented. At least once a year after the start of the study, the ethics review committee shall be informed of the continuation of the study.

The principal investigator at each participating center will initiate the study after obtaining the approval of the ethics review committee of each participating center. In the case of a facility that does not have an ethics review committee, an external ethics review committee designated by the facility concerned or an external ethics review committee designated by the study sponsor or an ethics review committee at the cardiovascular research institute shall be subject to executive deliberations.

## Expected benefits to the study audience

Since this study is a registry study that uses approved drugs within the scope of indications, there is no change in treatment policy by study subjects to participate in this study, and there is no specific benefit from participating in this study. Findings from this study are expected to benefit future patients with AF, including those studied.

## Potential risks and disadvantages to the study population

This study prospectively observes the current treatment status of late-stage elderly patients with NVAF, and no treatment-related adverse events are other than those that can occur with conventional treatment in general practice. In addition, blood sampling, examinations, and survey questionnaires administered to the study subjects do not deviate from the range of therapeutic normally performed in general practice.

## Compensation for health damage

This is a prospective observational study in general practice. If any health damage occurs after participation in this study, in principle, the health insurance provided by the research subject will be used to treat the health damage, and the cost of treatment will not be paid to the research subject from the research institution.

In the event of a health hazard, the principal investigator, etc., of the study institution shall promptly take treatment and other necessary measures. Health hazards caused by adverse reactions that occur after administration and dosage according to the instructions of the principal investigator, etc. are subject to the application for relief benefits under the Relief System for Sufferers from Adverse Drug Reactions.

The sponsor will also purchase clinical research insurance for health damages caused by the study as compensation or liability for health disorder during the study period, and as compensation for health damage caused by the study plan (death, sequelae class 1 or 2).

